### Interventions

Wrist-ankle acupuncture (WAA) is a unique acupuncture method. According to the principle of point selection of WAA, insomnia is a symptom that cannot be located. When doing wrist-ankle acupuncture, we choose upper 1 on both sides [11]. In the acupressure wrist-ankle strap group, the compression component of the wrist-ankle strap compresses upper 1 to produce an acupuncture-like effect. (Figs. 2 and 3)

**Fig. 2 Fig2:**
[figure not shown]
Wrist-ankle acupuncture (WAA) zones and needling points

**Fig. 3 Fig3:**
[figure not shown]
Location of the upper 1 point of wrist-ankle acupuncture (WAA)

The acupressure wrist-ankle strap is a device developed based on WAA therapy (Fig. 4), which is used to replace the invasive operation of WAA. The compression part of the wrist-ankle strap, which is detachable, is used to apply pressure and stimulation to the corresponding WAA point (compression point) to achieve the effect of treating diseases. There is a compression component mounting base on the wrist-ankle strap, and the position can be adjusted according to the needs of the disease, and then 1 to 2 compression components can be installed. Compressing different points can alleviate the pain in different body regions and is usually used for pain, insomnia, motion sickness, seasickness, morning sickness, etc.

**Fig. 4 Fig4:**
[figure not shown]
The acupressure wrist-ankle strap and its accessories

#### Acupressure wrist-ankle strap group

This group is the intervention group. A portable WAA' point compression therapy device is used, with compression components inside; the bilateral upper 1 are selected as the compression points. The upper 1 is located at the depression between medial border of the ulnar and the tendon of musculus flexor carpi ulnaris, the level of about two fingers above the transverse crease of the wrist. A compression component is installed inside the wrist-ankle strap and worn on both wrists to ensure that the compression component can be compressed to the upper 1 compression point, as shown in Fig. 5. Wear it for 30 min before going to bed every day, and take it off at bedtime, 2 weeks as a course of treatment, four courses in total. The acupressure wrist-ankle strap compression device is shown in Fig. 6A.

**Fig. 5 Fig5:**
[figure not shown]
The acupressure wrist-ankle straps on bilateral upper 1

**Fig. 6 Fig6:**
[figure not shown]
The acupressure wrist-ankle strap compression device is shown in **A**, the non-acupressure wrist-ankle strap compression device is shown in **B**

#### Non-acupressure wrist-ankle strap group

This group served as the control group. A portable WAA' point compression therapy device is selected. The inner compression component will automatically contract without compression, and it will be worn at the same position on both wrists. Wear it for 30 min before going to bed every day, and take it off at bedtime. 2 weeks as a course of treatment, four courses in total. The non-acupressure wrist-ankle strap compression device is shown in Fig. 6B.

After the patients are determined to participate in the study, a trained person will be responsible for guiding upper 1. Daily attendance on the smartphone app will be adopted to ensure that participants wear it every day. At the end of each course, the wearing condition of the strap will be followed up by telephone.

In addition, all patients will be given CBTI. CBTI has achieved widespread scientific recognition as an effective treatment for a wide variety of insomnias. This approach can effectively correct the wrong sleep cognition and inappropriate behavior factors of patients with insomnia [19]. The study adopts the treatment proposed by Michael L. Perlis in *Cognitive-behavioral treatment of insomnia: A session-by-session guide*, including stimulus control therapy, sleep restriction therapy, sleep hygiene education, and cognitive therapy [20]. The treatment is conducted systematically and requires therapist-patient dialogues every week (face-to-face or telephone-based dialogues), eight times in total, as a course of treatment. CBTI will be implemented by two professional therapists trained in clinical sleep medicine programs and had psychological qualifications.

### Outcomes

The schedule of enrolment, interventions, and assessments is shown in Fig. 7. The following outcomes for all the patients will be assessed in person by blinded and independent assessors.

**Fig. 7 Fig7:**
[figure not shown]
The schedule of enrolments, allocation, and assessments

#### Primary outcome

The primary outcome is the Pittsburgh sleep quality index (PSQI) global score, which evaluates a patient's general sleep quality in the past month. The PSQI consists of 19 self-assessment questions and 5 questions assessed by sleep partners. Only 19 self-assessment questions will be scored. The 19 self-assessment questions constitute seven factors from 0 to 3 points. The cumulative score of each factor component is the total score of the PSQI. The total score ranges from 0 to 21. A higher score means worse sleep quality [21]. The PSQI will be assessed at baseline, 4, 8 weeks after randomization and follow-up period.

#### Secondary outcomes

##### PSQI component scores

The PSQI component scores include seven domains, using 0, 1, 2, and 3 points to evaluate the patient's duration of sleep, sleep disturbance, sleep-onset latency, daytime dysfunction due to night sleep, sleep efficiency, need for medications to sleep, and overall sleep quality [17], which will be assessed at baseline, 4, 8 weeks after randomization and follow-up period.

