### Statistical analysis

Participants will complete relevant questionnaires and laboratory tests at the first visit. Researchers will guide to ensure the reliability and validity of the questionnaire; meanwhile, a sleep monitor will be completed before the treatment.

All observation results will be documented in the clinical observation forms. Missing data will be replaced according to the principle of LOCF (the last observation carried forward). At the same time, a computer database will be established. The obtained data will be input into the computer on the day of observation records. SPSS 21.0 will be used for statistical processing. Measurement data will be summarized by descriptive statistics (mean, standard deviation (SD), median and interquartile), count data use frequency tables (frequencies and percentages). Normal distribution test and homogeneity test of variance are performed on measurement data. The baseline characteristics of the two groups will be analyzed using independent samples *t* test or Mann-Whitney *U* test (if the distribution was not normal or the variance not homogeneous). If the baseline characteristics are imbalanced, covariance analysis is used to adjust the data. We will use an independent sample *t* test for comparison of between-group comparison and paired sample *t* test for comparison within each group after data meeting normal distribution test and homogeneity test of variance, otherwise using Mann-Whitney *U* test and Wilcoxon signed-rank test. The Pearson chi-square will be performed to compare count data. All statistical tests will be conducted at a 2-tailed significance level of 5%.

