In this trial, the patients with mild insomnia prefer physical therapy rather than medication, and there is no high risk without other treatments. Therefore, it is ethically possible for us to include a control group that receives just CBTI. This trial is a rigorously designed randomized controlled, double-blind trial. The design of the non-acupressure wrist-ankle strap, the wrist-ankle strap instruction manual, and follow-up appointments ensure the accuracy of the blind method of this trial. To ensure the quality of this research, before the research officially starts, we conducted a pre-experiment first, consult experts and literature to optimize the test plan based on the pre-test situation, and submitted the study protocol to the medical ethics committee for review and approval; each stage of the trial has an independent researcher to supervise the subject and collect feedback in time; all the research participants, including researchers, receptionists, and data processors, will be trained to ensure the smooth implementation of the trial.

The study aims to provide evidence-based medical evidence for the prevention and treatment of insomnia by acupressure wrist-ankle strap and promotes WAA clinical application. The result of this trial is expected to confirm that the new type of acupressure wrist-ankle strap can significantly improve the sleep quality and anxiety disorder of patients, reduce the suffering of patients, and improve the quality of life; it can also shorten the latency to fall asleep, increase the total sleep time, reduce the number of arousals and duration, improve sleep efficiency; it can reduce ACTH, CORT, 5-HT, and NA in the peripheral blood of patients with insomnia, thereby improving sleep quality.

In view of the above considerations, this study intends to sort out and summarize the clinical data of the new type of acupressure wrist-ankle strap for mild insomnia patients with anxiety disorder in this research group and form a standardized treatment plan. A strictly designed randomized controlled study method will be used to compare the improvement of acupressure wrist-ankle strap and non-acupressure wrist-ankle strap on the patients, to verify its efficacy further and explore the possible mechanism of action, to enrich the treatment of insomnia, improve its clinical efficacy, and lay the foundation for the popularization and application of the acupressure wrist-ankle strap.

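### The PSQI sleep-medication component starts at or near zero, so it can register only new drug use, and withdrawal followed by LOCF hides part of that

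*Protocol article*

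**What the plan says.** The section on PSQI component scores names seven domains, each scored 0 to 3. One is "need for medications to sleep", and the set is one "which will be assessed at baseline, 4, 8 weeks after randomization and follow-up period". The Primary outcome section describes the PSQI as measuring "general sleep quality in the past month".

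The Exclusion criteria bar anyone who used a hypnotic or sedative in the month before entry. Under the Dropout criteria, one route by which patients leave of their own accord is taking such a drug on their own initiative and themselves asking to withdraw.

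The Statistical analysis section states: "Missing data will be replaced according to the principle of LOCF (the last observation carried forward". It goes on: "We will use an independent sample *t* test for comparison of between-group comparison and paired sample *t* test for comparison within each group", with Mann-Whitney and Wilcoxon tests as fallback and a Pearson chi-square for counts. No component is treated differently.

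**The concern.** The recall window of the scale and the drug-free window required at entry are the same length. A component that asks about sleep medication over that window therefore has a floor at baseline, and a paired test on it can find no change or worsening, never improvement.

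What it can still show is whether one arm takes up drugs more than the other. That matters here: the Background presents the strap as a substitute for drug treatment, so starting a hypnotic is a natural failure event. Among the outcomes the article lists, this component is the only one described as registering drug use. Yet the patients most likely to score on it may leave before they are scored, and the imputation rule then gives them the score of a patient who needed no drug.

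**Working it through.** **The plan's own figure.** The document gives no number for this component. The number per arm used below comes from the Sample size section and reproduces. With difference 8.625 − 6.125 = 2.5 and SD 3.60, the printed formula gives 2 × (3.60 × (1.96 + 1.28) / 2.5)² = 43.5, so 44. A t-test calculation gives 45 (power 0.903; 0.896 at 44). Then 45 / 0.8 = 56.25, so 57 per arm and 114 in total.

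**Baseline.** No hypnotic or sedative in the past month, together with past-month recall, puts the component at 0 or very close to it. The other six components give at most 6 × 3 = 18 of the scale's 21 points at entry.

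**After baseline, three kinds of drug starter.**
1. Stays and is assessed: scored 1 to 3, so the event is seen.
2. Leaves before the next PSQI: LOCF carries forward the score from before the drug, normally 0, so the event is recorded as its absence.
3. Is assessed after starting and leaves later: a positive score is carried forward, so the event is kept.

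The loss comes from the second kind.

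**Size of the loss.** The rates of starting a drug are assumptions, because the document gives none. Let p_C and p_A be the proportions starting in the control and active arms, and w the share of starters who leave unscored. Starters who stay score 1, 2 or 3 with equal chance (mean 2). The expected difference in component means is

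2 × (p_C − p_A) × (1 − w).

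For 20% v 5% with w = 0.5 this is 2 × 0.15 × 0.5 = 0.15. Power was simulated with 57 per arm and a two-sided Mann-Whitney test at 0.05 (4,000 runs):

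| Starters, control v active | w = 0 | w = 0.5 | w = 0.8 | w = 1 |
|---|---|---|---|---|
| 10% v 3% | 0.32 | 0.14 | 0.02 | 0 |
| 20% v 5% | 0.70 | 0.38 | 0.12 | 0 |
| 30% v 10% | 0.77 | 0.44 | 0.16 | 0 |

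In the middle row about 0.20 × 57 = 11.4 controls and 0.05 × 57 = 2.9 active patients start a drug. With w = 0.5, only 5.7 and 1.4 of them are visible in the score. In the bottom row (0.30 + 0.10) × 57 = 22.8 patients start, so w = 1 there would use up the whole planned dropout of 0.20 × 114 = 22.8.

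**What counting every starter restores.** For a comparison of proportions, power is about Φ{[(p_C − p_A) − 1.96 × SE₀] / SE₁}, with SE₀ = √(2p̄(1 − p̄)/57) and SE₁ = √((p_C(1 − p_C) + p_A(1 − p_A))/57). For 20% v 5%: p̄ = 0.125, SE₀ = 0.0620, SE₁ = 0.0603, and (0.15 − 0.1214)/0.0603 = 0.47, so power is about 0.68. The same formula gives about 0.33 for 10% v 3% and 0.77 for 30% v 10%. These match the w = 0 column and do not depend on w, provided drug use is known for those who leave.

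**The case against.** A reader might infer that this component cannot show benefit at all, or carries no information. The documents do not support that. The entry rule restricts the baseline score only. The component is scored again at weeks 4 and 8 and at follow-up and is compared between arms, so less new drug use with the active strap would be a benefit it can show. Its power reaches zero only if every starter leaves unscored. Even the zero at baseline is an inference, since a sleep product outside the exclusion's wording could score above 0.

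A reader might also infer that drug use by those who stay makes the strap look effective. That requires more use in the active arm. If the strap works, use could be higher among controls, whose scores would then improve and hide a benefit. The direction is open.

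The number affected may be small. The Discussion says these patients "prefer physical therapy rather than medication", and the document does not split the 20% dropout by reason. Supposing that a quarter to a half of the 22.8 dropouts started a drug gives 6 to 11 patients, but that share is an assumption and should not be presented as an estimate.

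Finally, reporting all seven components is legitimate, and a condensed article need not describe how concomitant drugs are recorded. Both points stand. Neither removes the problem, which lies in stated rules: the dropout wording and LOCF together assign a wrong value to a listed outcome.

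**Conclusion.** The point holds in a limited form. The medication component has a floor at entry, so within-group improvement on it is impossible. Its between-arm contrast survives but is weakened by withdrawal followed by LOCF. Under the assumed starting rates, power is 0.32 to 0.77 if all starters stay, 0.14 to 0.44 if half leave unscored, and 0 if all do. The true loss is unknown.

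For starters who stay, the global PSQI mixes drug and strap effects: the drug can add at most 3 points on this component while it may lower others. No direction of bias in the primary outcome can be claimed. All of this rests on reading the dropout wording as written, so that taking a drug without asking to leave does not end participation.

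**What to change.** For this component, do not rely on the LOCF-filled score. Compare between arms the proportion of all randomised patients who took any hypnotic or sedative from randomisation to each visit, counting those who withdrew for that reason, with the chi-square test already planned for counts.

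Collect use in the existing telephone call at the end of each course and at the PSQI visits. The calls end with treatment, so the visits are needed to cover follow-up. For those who leave, take it from the withdrawal reason, which the Dropout criteria already distinguish. Patients who simply stop attending will have unknown use, and their number should be given by arm.

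Keep the global PSQI score as planned. Add the sum of the other six components by randomised arm as a sensitivity analysis. Do not split it by drug use: use arises after randomisation and may itself be affected by treatment, so such a split would lose the protection of randomisation.

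The cost is one extra data field and a binary comparison in place of one listed component test. As recruitment has begun, the change should be dated and documented. It concerns measurement and analysis only and alters no rule on drug use or on staying in treatment.

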##### Hamilton Anxiety Scale (HAMA)

The HAMA is a commonly used scale in psychiatric clinics, including 14 items. As an important diagnostic tool for anxiety disorders, it is often used clinically as a basis for the diagnosis and degree classification of anxiety disorders. According to the relevant data of the scale, if the score is less than 7, there is no anxiety; if the score is more than 7, there may be anxiety; if the score is more than 14, there must be anxiety; if the score exceeds 21 points, there must be evident anxiety; if the total score exceeds 29 points, it may be severe anxiety. If the scale score is more than 14, it can be diagnosed as an anxiety disorder [18]. HAMA will be examined jointly by two trained assessors. The method of conversation and observation is adopted. Before the start of the clinical trial, the assessors have received 1-week of scale evaluation training by experts to uniform evaluation terms and standardize the evaluation process. The two assessors score independently, and the mean scores will be taken. HAMA will be assessed at baseline, 4, 8 weeks after randomization and follow-up period.

##### wActiSleep-BT monitor

The Actigraphy is a small-sized wristwatch worn on the patient’s wrist before going to bed. It can monitor sleep quality, such as the latency to fall asleep, total sleep time, number and duration of wake-ups, and sleep efficiency. The main sleep parameters are sleep efficiency (SE), total sleep time (TST), and wake after sleep onset (WASO). It will be assessed at baseline, 4, 8 weeks after randomization and follow-up period. Record the value of three consecutive days for each measurement. Values with significant errors will be discarded and take the average value for comparison.

##### Laboratory tests

The pathogenesis of insomnia is that some substances in the brain (such as neurotransmitters, hormones, etc.) act on the sleep center of the human body under the influence of various factors, leading to the abnormality of the central neurotransmitter, and then affect sleep. There is some evidence [6, 7] that the pathogenesis of insomnia is closely related to the circadian secretion of peripheral blood-related hormones in the hypothalamic-pituitary-adrenal axis (HPA axis). In this study, we will detect the levels of adrenocorticotropic hormone (ACTH), cortisol (CORT), serotonin (5-HT), norepinephrine (NE) before and after treatment in the two groups. Participants will receive blood tests in the clinical laboratory of the hospital (items: ACTH, CORT, 5-HT, NE, examination time: 8 a.m., fasting state, venous blood of upper limb), and blood test report issued within five working days by the hospital. The blood tests will be measured at baseline and the 8th week. The laboratory test report will be kept and recorded by an independent data manager.

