**Methods/design:**

This trial is a parallel-design, patients-assessor blinded, randomized, sham-controlled. In total, 114 patients diagnosed with mild insomnia and anxiety disorders will be randomly assigned into two groups, the acupressure wrist-ankle strap group or the non-acupressure wrist-ankle strap group; they will receive treatments for eight weeks with five sessions each week. Rating scales, sleep monitors, and laboratory tests will be used to observe the clinical effect. From the perspective of the circadian secretion of peripheral blood-related hormones in the hypothalamic-pituitary-adrenal (HPA) axis, the possible mechanism of acupressure wrist-ankle straps for treating insomnia is studied.

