**Discussion:**

The results of this study will confirm the efficacy of acupressure wrist-ankle strap in treating mild insomnia patients with anxiety disorder and whether its mechanism is related to the HPA axis. The acupressure wrist-ankle strap may become a pure physical, no side effect treatment of mild insomnia.

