## Methods/design

### Study design

This study is a two-armed, double-blind, randomized, sham-controlled clinical trial aiming to explore the efficacy of the acupressure wrist-ankle strap for insomnia patients with anxiety disorder.

A total of 114 participants, from the department of acupuncture and moxibustion and the department of internal medicine of traditional Chinese medicine of Shanghai Changhai Hospital, diagnosed with mild insomnia and anxiety disorder following *Guidelines for the Diagnosis and Treatment of Insomnia in China* formulated by the Chinese Sleep Medicine Congress (CSMC, 2017 revised version) [3] and *Expert Consensus on Diagnosis and Treatment of Anxiety and Depression in General Hospitals* formulated by Anxiety disorder cooperation group, Psychiatry Branch, Chinese Medical Association (2012 revised version) [15] will be randomly assigned to two equal groups with 57 patients in each group, including acupressure and non-acupressure wrist-ankle strap group. The outcomes include scales, objective parameters detected by device (wActiSleep-BT Actigraph equipment), and laboratory tests, which will be used to observe the efficacy of the strap on insomnia patients and study its possible mechanism of circadian secretion of related hormones in peripheral blood of hypothalamic-pituitary-adrenal axis (HPA axis). Our study will last 13 weeks in total. The protocol has been registered on the Chinese Clinical Trial Registry (identifier: ChiCTR2000039352) and will be conducted following the Helsinki declaration. This trial will be reported according to the Consolidated Standards of Reporting Trials (CONSORT) statement [16]. The study flowchart is summarized in Fig. 1.

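### The article says it studies circadian secretion of HPA-axis hormones, but one fasting 8 a.m. sample at baseline and one at week 8 can only compare morning levels

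*Protocol article*

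**What the plan says.** **Aim.** The abstract (Methods/design) introduces the mechanistic part of the trial with the words "From the perspective of the circadian secretion of peripheral blood-related hormones in the hypothalamic-pituitary-adrenal (HPA) axis". The Study design section says that the outcomes will serve to "study its possible mechanism of circadian secretion of related hormones in peripheral blood of hypothalamic-pituitary-adrenal axis". These are the two places where the aim itself is worded as circadian. The Laboratory tests section also mentions circadian secretion, but as background on the pathogenesis of insomnia.

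**Measurement.** The Laboratory tests section names four analytes (ACTH, cortisol, 5-HT, NE) and says that their levels will be measured before and after treatment. It fixes the draw as "examination time: 8 a.m., fasting state, venous blood of upper limb" and the visits as "The blood tests will be measured at baseline and the 8th week". The paragraph that closes the list of secondary outcomes, after the TCM syndrome scale, repeats those two visits. The text describes no second clock time, no serial sampling and no rhythm parameter.

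**Planned conclusion.** The abstract's Discussion says the results will confirm efficacy and also "whether its mechanism is related to the HPA axis". The main Discussion expects the strap to lower the four analytes in peripheral blood and presents that reduction as the route by which sleep improves.

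**The concern.** The stated aim concerns how hormone secretion varies over the day. The planned samples all come from the same hour. Fixing the hour holds time-of-day variation constant, which is good practice for comparing levels, but it also means that the data carry no information about that variation.

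What is at stake is how the laboratory results may be read. If the arms differ at 8 a.m., the difference cannot be attributed to a changed rhythm. If they do not differ, a real change in rhythm could still be present. Under the aim as worded, either result could be taken as evidence on circadian secretion, and neither would be.

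**Working it through.** There is no figure in the plan to reproduce on this point. The sample size rests on PSQI alone and has no bearing here. The check is whether the sampling times can identify a rhythm.

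**Inputs**
- Clock times per sampling day: one, 8 a.m. (Laboratory tests).
- Sampling visits: two, baseline and week 8 (Laboratory tests; closing paragraph of the secondary outcomes).
- Rhythm model: the simplest usual one, a single 24-hour cosine. This is my assumption. A richer model has more unknowns and would fare worse.

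**Step 1: the model.** With M the 24-hour mean, A the amplitude and φ the time of the peak,

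y(t) = M + A·cos(2π(t − φ)/24) = M + b·cos(2πt/24) + c·sin(2πt/24).

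Each visit has three unknowns: M, b and c, or equivalently M, A and φ. They can be estimated only if the matrix with rows [1, cos(2πt/24), sin(2πt/24)] at the sampled times has rank 3.

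**Step 2: rank by sampling scheme**

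| Clock times | Rank (of 3) | What can be estimated |
|---|---|---|
| 8 a.m. | 1 | the 8 a.m. level only |
| 8 a.m., repeated at week 8 | 1 | the 8 a.m. level only |
| 8 a.m. and 8 p.m. | 2 | a day-night difference; amplitude and phase not separable |
| 8 a.m., 4 p.m., midnight | 3 | mean, amplitude and phase |

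The planned scheme is the second row. Two clock times would give a slope, and a cosine fit needs at least three.

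**Step 3: worked example.** Units and values are assumed for illustration. At baseline take M = 10, A = 5 and peak at 8 a.m., so y(8) = 10 + 5 = 15. Three different changes then give the same reading:
- mean falls by 2: 8 + 5 = 13;
- amplitude falls by 2: 10 + 3 = 13;
- peak shifts by d hours, mean and amplitude unchanged: 10 + 5·cos(2πd/24) = 13 requires cos(2πd/24) = 0.6, so d = (24/2π)·arccos(0.6) ≈ 3.54 hours.

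The reverse also occurs. If the mean rises by 2 while the amplitude falls by 2, then y(8) = 12 + 3 = 15, the same as baseline, although the rhythm has changed.

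**Step 4: does sample size help?** No. More patients reduce the standard error of the mean 8 a.m. level in each arm, but they add no second clock time. The ambiguity is one of identification, not of precision.

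**The case against.** The best defence is that this is a matter of vocabulary. The Laboratory tests section says that levels will be measured, which is what the sampling delivers. The only laboratory result the Discussion anticipates is a fall in levels, and no rhythm parameter is listed as an outcome. The abstract and the Study design section call the mechanism only a possible one, the laboratory tests are secondary, and a fixed fasting hour is sound practice.

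Much of this stands. It shows that the measurement is sensible and that the fault lies in the stated aim. It does not remove the mismatch, because the abstract and the Study design section still name circadian secretion as what is being studied. Nor can the gap be put down to condensation for a journal: the article gives the analytes, hour, fasting state, vein and visits. The schedule figure is not available, but the text fixes the visits twice.

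Three stronger readings are tempting, and the documents do not support them.
- A reader might infer that the trial can say nothing about the HPA axis. It can say something: a randomised comparison of ACTH and cortisol at a fixed hour is valid, limited evidence on morning levels.
- A reader might infer that the circadian claim runs through the whole article. The abstract's Discussion speaks only of the HPA axis, and the Laboratory tests section uses the term as background.
- A reader might fault the absence of an analysis linking hormone change to PSQI change. That is commonly left to a statistical analysis plan, which is not shown here, so its absence from the article is not a finding. Multiplicity across the four analytes is a separate matter and does not measure this defect.

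**Conclusion.** The point holds as a mismatch between aim and measurement. With one clock time the design has rank 1 of 3 for a daily rhythm, at each visit and across both, so a change in 24-hour mean, amplitude or phase cannot be told apart. No statement about circadian secretion can follow from these samples, whichever way the result falls.

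The reach is limited. The primary outcome, the sample size and the between-arm comparison of 8 a.m. levels are unaffected; what must narrow is the mechanistic claim. The conclusion assumes that the sampling described in the text is complete. It does not depend on the numbers in the illustration: any daily rhythm with more than one unknown is unidentified from a single clock time.

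**What to change.** 1. **Aim (abstract, Methods/design; Study design).** Remove the reference to circadian secretion. State the mechanistic aim as the between-arm difference in fasting 8 a.m. ACTH, cortisol, 5-HT and NE at week 8, with the baseline value of each analyte as covariate. The covariate is a side improvement: the Statistical analysis section now adjusts only if baseline proves imbalanced.
2. **Conclusion (abstract, Discussion; main Discussion).** Limit the mechanistic conclusion to exploratory evidence on morning levels. Drop the promise to confirm a mechanism, and drop the wording that makes lower hormone levels the cause of better sleep.

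The cost is a narrower mechanistic claim and a few edited sentences. No additional blood draws, visits or patients are needed. If the sponsor wishes to keep a circadian aim, the wording change will not be enough: draws at three or more distinct clock times per sampling day would be required for a cosine fit.
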